### Outcomes

The primary outcome is the proportion of participants achieving simultaneous control of blood pressure, lipids, and glycemia at 12 months, defined as SBP of <130 mm Hg and diastolic blood pressure of <80 mm Hg, LDL-C of <2.6 mmol/L, fasting plasma glucose of <7.0 mmol/L, and HbA_1c_ of <7% (Table 1). Secondary outcomes include (1) clinical measures (changes in estimated 10-year CVD risk [GBCS model]; mean changes in SBP, LDL-C, triglycerides, fasting plasma glucose, and HbA_1c_; and the proportion achieving control of individual risk factors at 12 months), (2) behavioral measures (medication adherence and adoption of lifestyle modifications), (3) system-level outcomes (participant engagement with the CardioCare system and usability and satisfaction among participants and physicians), and (4) economic outcomes (incremental cost-effectiveness expressed as cost per participant achieving triple risk factor control and per quality-adjusted life year [QALY] gained; Table 1).

Medication adherence and lifestyle modifications (diet, physical activity, and smoking) will be assessed using structured questionnaires adapted from previously validated tools applied in chronic disease studies in Chinese populations. Measurements for all primary and secondary outcomes will be taken at baseline and 6 and 12 months after enrollment. To assess feasibility and acceptability, we will evaluate (1) recruitment rate (participants enrolled and approached); (2) retention rate at 12 months; (3) system engagement metrics, including number of messages opened and responded to; and (4) participant-reported usability and satisfaction at 12 months. Usability will be assessed using the System Usability Scale, and satisfaction will be measured using a 5-point Likert scale. These data will inform scalability potential and guide future implementation strategies. Quantitative feasibility metrics will be summarized descriptively, and comparisons between groups will be exploratory.

In addition to formal clinical and behavioral assessments at baseline and 6 and 12 months, the CardioCare system captures weekly engagement data, including message delivery, read status, interaction frequency, and responsiveness. These metrics will be used to construct engagement trajectories and assess temporal patterns of system use. The economic evaluation will be conducted from the health care system perspective. Direct medical costs will include personnel time, digital intervention costs (eg, system maintenance and messaging), outpatient visits, medications, and laboratory tests. Cost-effectiveness will be assessed through incremental cost-effectiveness ratios reported as cost per participant achieving triple risk factor control and per QALY gained.

**Table 1. T1:** Outcome measure summary.

Outcome	Definition and measure	Time point	Assessment method
Primary outcome	Triple risk factor control (SBP^a^ of <130 mm Hg, DBP^b^ of <80 mm Hg, LDL-C^c^ of <2.6 mmol/L, and HbA_1c_^d^ of <7%)	12 months	Clinical measurements and laboratory assays
Secondary outcomes			
10-year CVD^e^ risk	Estimated via GBCS^f^ model	Baseline and 12 months	Model-based calculation
SBP, LDL-C, HbA_1c_, FPG^g^, and triglycerides	Individual clinical parameters	Baseline and 6 and 12 months	Hospital-certified laboratory and digital BP^h^ monitor
Medication adherence	Self-reported adherence (structured questionnaire)	6 and 12 months	Validated adherence scale
Lifestyle modification	Diet, physical activity, and smoking status	6 and 12 months	Structured behavioral questionnaire
System engagement	Frequency of interactions with the CardioCare system	Continuous	Digital system logs
Usability	Perceived ease of use	12 months	SUS^i^
Satisfaction	Overall satisfaction with the system	12 months	5-point Likert scale questionnaire
Cost-effectiveness	Cost per case of triple risk factor control and QALYs^j^ gained	Baseline and 12 months	Economic modeling using trial data

a SBP: systolic blood pressure.

b DBP: diastolic blood pressure.

c LDL-C: low-density lipoprotein cholesterol.

d HbA_1c_: glycated hemoglobin.

e CVD: cardiovascular disease.

f GBCS: Guangzhou Biobank Cohort Study.

g FPG: fasting plasma glucose.

h BP: blood pressure.

i SUS: System Usability Scale.

j QALY: quality-adjusted life year.

### Sample Size Estimation

The sample size was calculated to detect an absolute difference of 15 percentage points in the primary outcome (ie, 20% in the control group vs 35% in the intervention group), with 80% power and a 2-sided α of .05. This requires 126 participants per arm. Allowing for 15% attrition, the final target sample size is 300 participants (150 per group). This expected difference is based on previous studies in Chinese older adult populations showing triple risk factor control rates ranging from 15% to 25% under usual care and on effect sizes from similar multicomponent digital interventions, which have reported 10– to 20–percentage point improvements in risk factor control [14]. Recruitment will take place during routine health checkup visits, with eligible individuals identified from their health data and approached in person by a trained research assistant. Additional recruitment will be supported through study posters in the Health Management Center and announcements on the hospital’s WeChat platform.

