## Methods

### Participants

This single-center, 2-arm, parallel-group RCT with a 1:1 allocation ratio will be conducted at the Health Management Center of the First Affiliated Hospital of Sun Yat-sen University in Guangzhou, China (Figure 1). The trial is designed within a superiority framework to determine whether the CardioCare system is more effective than minimal usual care in achieving triple risk factor control at 12 months among high-risk adults.

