### Statistical Analysis

All analyses will follow the intention-to-treat principle, with all randomized participants included in the group to which they were assigned. The primary outcome will be compared between groups using a chi-square test, with risk differences and 95% CIs calculated. Secondary continuous outcomes will be analyzed using mixed-effects models adjusting for baseline values. Missing data patterns will be assessed visually and statistically (eg, the Little missing completely at random test) to inform appropriate imputation models. Multiple imputation using chained equations will be used under the assumption of the data being missing at random, and sensitivity analyses will include complete-case and worst-case scenarios. Prespecified subgroup analyses will examine potential effect modification by sex, age group, and baseline CVD risk. These subgroup analyses are exploratory in nature and will not be powered to detect statistically significant differences. Findings will be interpreted descriptively and used to inform hypothesis generation for future trials.

QALYs will be estimated using utility weights derived from published data on health-related quality of life in Chinese adults. A within-trial cost-effectiveness analysis will be conducted over the 12-month intervention period. Sensitivity analyses will be conducted to examine the robustness of the incremental cost-effectiveness ratio to variations in key cost and outcome inputs. All analyses will be conducted using Stata (version 18.0; StataCorp). A 2-sided *P* value of <.05 will be considered statistically significant.

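### The stated 126 per arm does not give 80% power for 20% versus 35%: standard formulas need 136 to 138, and 300 randomised with 15% attrition gives about 77%

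*Protocol article*

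**What the plan says.** All the inputs are in the protocol article, and all but the allocation ratio and the test are in one paragraph.

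- **Effect** (Sample Size Estimation): an "absolute difference of 15 percentage points in the primary outcome", specified as "20% in the control group vs 35% in the intervention group".
- **Error rates** (Sample Size Estimation): "with 80% power and a 2-sided α of .05".
- **Result** (Sample Size Estimation): "This requires 126 participants per arm".
- **Target** (Sample Size Estimation): "Allowing for 15% attrition, the final target sample size is 300 participants (150 per group").
- **Design** (Participants): "parallel-group RCT with a 1:1 allocation ratio".
- **Primary test** (Statistical Analysis): "The primary outcome will be compared between groups using a chi-square test, with risk differences and 95% CIs calculated".

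No interim analysis is planned (Monitoring), so no alpha is spent elsewhere. Baseline adjustment is mentioned only for the secondary continuous outcomes.

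**The concern.** The inputs are complete and the result can be checked directly. The usual uncorrected formulas for two proportions differ from each other by only one or two participants per arm here, yet the printed figure lies 10 to 12 below all of them. The choice of formula therefore does not explain the gap.

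The stated power of the primary comparison is at stake. If 126 is too small, the 300 derived from it is also too small for the 80% claimed at the planned attrition. The trial would then run a higher risk of missing a true 15-point effect than its readers are told.

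**Working it through.** **Inputs.** p₁ = 0.20, p₂ = 0.35, difference 0.15, two-sided α = 0.05 (z = 1.960), power 80% (z = 0.8416), equal arms, chi-square test. Then p̄ = 0.275 and p₁(1−p₁) + p₂(1−p₂) = 0.16 + 0.2275 = 0.3875.

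**Can 126 be reproduced?** Required number per arm, two-sided:

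| Method | Calculation | n per arm |
|---|---|---|
| Pooled variance (matches the chi-square test) | [1.960·√(2·0.275·0.725) + 0.8416·√0.3875]² / 0.15² = (1.2377 + 0.5239)² / 0.0225 = 137.9 | 138 |
| Unpooled variance | (2.8016)² · 0.3875 / 0.0225 = 135.2 | 136 |
| Arcsine | 2·(2.8016)² / 0.3388² = 136.8 | 137 |
| Average-p variance in both terms | 2·(2.8016)² · 0.275 · 0.725 / 0.0225 = 139.1 | 140 |
| Continuity-corrected | (137.9/4)·[1 + √(1 + 4/(137.9·0.15))]² = 150.95 | 151 |

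None gives 126. A one-sided 5% test would need 107 (unpooled), 108 (arcsine), 109 (pooled) or 122 (continuity-corrected). None of these matches either, and a one-sided test would contradict the stated sidedness. The pooled formula returns 126 if power is set to 76%. Against 138, the stated figure is short by 12, and 12/138 = 8.7%.

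**Attrition step.** 126/0.85 = 148.2, so 149, taken up to 150. This step is correct, so the fault lies only in the base figure. The same step from 138 gives 138/0.85 = 162.4, so 163 per arm (326 in total). From 136 it gives 160 per arm (320 in total).

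**Power actually available.** Pooled formula: power = Φ{[0.15·√n − 1.2377] / √0.3875}.

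- n = 126: (1.6837 − 1.2377)/0.6225 = 0.717, power 76.3%.
- n = 127.5 (150 × 0.85): (1.6937 − 1.2377)/0.6225 = 0.733, power 76.8%.
- n = 138: power 80.0%.
- n = 150 (no attrition): power 83.2%.

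Exact binomial enumeration of the uncorrected chi-square test gives 76.7% at 126, 77.1% at 127, 77.5% at 128, 80.0% at 136 and 80.3% at 138.

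**Detectable difference.** With a 20% control rate and 127 to 128 evaluable per arm, 80% power is reached at a difference of about 15.7 points (15.6 to 15.7 by the pooled formula).

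**Attrition that 300 can absorb.** 1 − 138/150 = 8.0% by the pooled formula. By exact enumeration it is 1 − 136/150 = 9.3%.

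**Across the usual-care range that the section cites (15% to 25%).** With a 15-point difference and about 127 evaluable per arm, power is about 82% for 15% versus 30%, about 77% for 20% versus 35%, and about 73% for 25% versus 40%.

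**The case against.** The strongest reply is that the loss is small: about 3 points of power, or 0.7 points of detectable difference. The uncertainty in the assumed rates moves power more than this, from about 73% to 82% over the control rates that the protocol itself cites. Type I error and the validity of the estimate are untouched, and the reported confidence interval will show the precision achieved whatever the design power was. All of this is true. It limits the size of the point but does not make the printed figure right.

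A second reply is that the analysis includes all randomised participants with multiple imputation, so that 77% is pessimistic. It is indeed a completers figure at exactly 15% attrition and should be labelled so. With no information lost, 150 per arm would give about 83%, and the 6-month measurements may recover something. But imputation cannot be assumed to restore all that is lost, and the protocol itself sizes on completers by inflating for attrition. In any case, this concerns the power of 300 randomised and not whether 126 evaluable per arm is the correct requirement.

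Third, the attrition limit depends on the formula: 8% is the pooled value and about 9% the exact one. That stands.

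A smaller number could be defended with a covariate-adjusted primary analysis, but the protocol specifies an unadjusted chi-square test and gives no prognostic strength from which a gain could be calculated.

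**Conclusion.** The point holds. With the stated inputs the requirement is 136 to 138 per arm without continuity correction, not 126, and 151 with it. At the planned 150 per arm and 15% attrition, power is about 77% (76.8% pooled, 77.1% to 77.5% exact at 127 to 128 per arm). The type II error for the primary comparison is therefore about 23% rather than 20%.

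These figures assume that the true rates are 20% and 35%, that attrition is 15% in each arm with no information recovered from those lost, and that the test is the uncorrected chi-square test named in the protocol. A continuity-corrected test would widen the gap. The shortfall is modest, but the sample size and power are wrong as written.

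**What to change.** Correct the Sample Size Estimation paragraph. The minimum change keeps the target of 300:

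> The pooled-variance formula requires 138 evaluable participants per arm. With 150 randomised per arm and 15% attrition (about 127 evaluable), the unadjusted chi-square test has about 77% power for 20% versus 35%, or 80% power for a difference of about 15.7 percentage points. Power of 80% for 15 points holds if attrition is at most 8%.

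It would help to add the power at both ends of the cited usual-care range (about 82% for 15% versus 30%, about 73% for 25% versus 40%).

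This costs one paragraph and a slightly less favourable stated power, with no extra participants.

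If the sponsor prefers to keep 80% power with 15% attrition, the target becomes 163 per arm, 326 in total (160 and 320 from the unpooled formula), which is 20 to 26 more participants. The article says that recruitment had not begun at submission, so either route was still open then. The choice is the sponsor's, but the per-arm figure, the power and the target must agree.

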### Data Collection and Management

Clinical and laboratory measurements will be collected at baseline and 6 and 12 months using standardized procedures. Blood pressure will be measured in duplicate using validated automated devices after 5 minutes of rest; the average reading will be recorded. Lipid profiles and glycemia will be measured in fasting venous samples analyzed at the hospital’s certified laboratory. Medication adherence will be evaluated using a self-administered online questionnaire. Lifestyle modification and system engagement data will be collected through structured questionnaires. All data will be entered into a secure, password-protected database, and automated range checks will be conducted. Regular audits will be conducted to ensure accuracy. Personal identifiers will be stored separately from trial data accessible only to authorized personnel.

### Statistical Analysis

All analyses will follow the intention-to-treat principle, with all randomized participants included in the group to which they were assigned. The primary outcome will be compared between groups using a chi-square test, with risk differences and 95% CIs calculated. Secondary continuous outcomes will be analyzed using mixed-effects models adjusting for baseline values. Missing data patterns will be assessed visually and statistically (eg, the Little missing completely at random test) to inform appropriate imputation models. Multiple imputation using chained equations will be used under the assumption of the data being missing at random, and sensitivity analyses will include complete-case and worst-case scenarios. Prespecified subgroup analyses will examine potential effect modification by sex, age group, and baseline CVD risk. These subgroup analyses are exploratory in nature and will not be powered to detect statistically significant differences. Findings will be interpreted descriptively and used to inform hypothesis generation for future trials.

QALYs will be estimated using utility weights derived from published data on health-related quality of life in Chinese adults. A within-trial cost-effectiveness analysis will be conducted over the 12-month intervention period. Sensitivity analyses will be conducted to examine the robustness of the incremental cost-effectiveness ratio to variations in key cost and outcome inputs. All analyses will be conducted using Stata (version 18.0; StataCorp). A 2-sided *P* value of <.05 will be considered statistically significant.

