### Random Allocation and Allocation Concealment

A statistician not involved in participant recruitment will generate the random allocation sequence using computer-generated random numbers. Randomization will be stratified by sex, with random block sizes ranging from 4 to 12 undisclosed to the recruitment team to ensure unpredictability. Allocation concealment will be maintained using sequentially numbered opaque, sealed envelopes prepared by staff independent of the enrollment process.

Research assistants will identify eligible participants, send invitations, and obtain informed consent, after which the next available envelope will be opened to reveal allocation. Personnel enrolling participants will not have access to the allocation sequence.

Participants and care providers will not be blinded due to the nature of the intervention. Outcome assessors and statisticians will remain blinded to allocation. Group codes will be masked during analysis, and the randomization key will only be revealed after the primary analysis is completed. No emergency unblinding procedures are required given the nonpharmacological nature of the intervention.

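### The primary comparison is an unadjusted chi-square test: valid, but it gives up precision that the baseline values already collected could supply

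*Protocol article*

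**What the plan says.** On the primary outcome, the Statistical Analysis section says: "The primary outcome will be compared between groups using a chi-square test, with risk differences and 95% CIs calculated". It names no covariate or stratum, and no adjusted analysis of the primary outcome appears elsewhere in the article.

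The information for adjustment is there:

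- Under Random Allocation and Allocation Concealment: "Randomization will be stratified by sex, with random block sizes ranging from 4 to 12".
- Under Outcomes: "Measurements for all primary and secondary outcomes will be taken at baseline and 6 and 12 months after enrollment". Data Collection and Management also places the clinical and laboratory measurements at baseline.
- The plan already adjusts elsewhere: "Secondary continuous outcomes will be analyzed using mixed-effects models adjusting for baseline values".

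Two further statements bear on the point. The analysis set is everyone randomised: "All analyses will follow the intention-to-treat principle, with all randomized participants included in the group to which they were assigned". For missing data, "Multiple imputation using chained equations will be used under the assumption of the data being missing at random", with complete-case and worst-case analyses kept for sensitivity.

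**The concern.** A binary outcome built from blood pressure, LDL-C and glycaemia is likely to depend on where each participant starts. The entry criteria in the Participants section are age, predicted risk above 10%, no previous CVD and a suitable mobile device. None requires a risk factor to be out of control, so some participants may already meet the primary endpoint at randomisation. Baseline status would then predict 12-month status, and a comparison that ignores it carries variance that could be removed at no cost in data.

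At stake is power for the one confirmatory test, and the width of the confidence interval for the risk difference. The plan adjusts its continuous secondary outcomes for baseline but not its primary outcome, the one that has to carry the conclusion.

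**Working it through.** **Inputs from the document.** Rates of "20% in the control group vs 35% in the intervention group", "with 80% power and a 2-sided α of .05", 126 per arm, 15% attrition, 150 randomised per arm. After attrition, 150 × 0.85 = 127.5, so about 127 evaluable per arm.

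**The plan's own figure.** For 20% v 35%, the standard two-sided calculation gives 138 per arm with a pooled variance and 136 with an unpooled one, not 126. At 126 per arm, power is 76.3%. That is a separate matter of sample size; here it only sets the starting level.

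**Unadjusted precision.** The variance term is 0.20 × 0.80 + 0.35 × 0.65 = 0.16 + 0.2275 = 0.3875. At 127 per arm, SE = √(0.3875/127) = 0.0552, and power ≈ Φ(0.15/0.0552 − 1.96) = 0.775 (0.766 with the pooled-variance formula).

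**Adjusted precision, under assumptions.** Let π be the share controlled at baseline. Let d be the difference in 12-month control between participants who were and were not controlled at baseline, taken as equal in both arms, with a 15-point effect in each baseline group. Removing the between-group part in both arms lowers the variance term by 2π(1 − π)d². With π = 0.20 and a control rate of 20%, phi in the control arm equals d.

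| Persistent / new control, control arm | phi | Variance term | Ratio to 0.3875 | Power at 127 per arm, formula | Simulated |
|---|---|---|---|---|---|
| 40% / 15% | 0.25 | 0.3875 − 0.32 × 0.0625 = 0.3675 | 0.948 | 0.796 | 0.791 |
| 50% / 12.5% | 0.375 | 0.3875 − 0.32 × 0.1406 = 0.3425 | 0.884 | 0.823 | 0.819 |
| 60% / 10% | 0.50 | 0.3875 − 0.32 × 0.25 = 0.3075 | 0.794 | 0.862 | 0.861 |

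The simulated column is a Cochran–Mantel–Haenszel test stratified by baseline status (20,000 runs). The chi-square test in the same simulation had power 0.77, and type I error of the stratified test was 4.9%.

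**Less favourable inputs, same formula, 127 per arm.**

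- π = 0.10, persistence 40%: d = 0.222, variance falls 2%, power 78%.
- π = 0.05, persistence 60%: d = 0.421, variance falls 4%, power 79%.
- π = 0.05, persistence 40%: d = 0.211, variance falls 1%, power 78%.

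**Check with a different model.** One continuous baseline covariate was given a latent correlation ρ with the outcome, together with a modest sex effect. The analysis was logistic regression with a standardised risk difference, at 126 per arm (1,500 runs per power scenario). Unadjusted power was about 77%. Stratifying by sex alone gave 77–78%. Adjusting for sex and baseline gave about 78%, 80%, 84% and 90% at ρ = 0, 0.3, 0.5 and 0.7.

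**Type I error.** In 8,000 null runs per scenario, the unadjusted test was at 4.7–5.0% and the adjusted model at 5.4%. A sparse model with sex and baseline control status held about 5.0–5.3%. A full model with control status plus all five component values ran at 5.4–5.9% at 127 per arm, against 4.4–5.1% for chi-square. Its power was only 78%, 78%, 80% and 84% at component correlations of 0, 0.3, 0.5 and 0.7.

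**The case against.** The strongest reply is that nothing here is wrong. An unadjusted comparison of two proportions is valid, is easy to read, and matches the sample-size calculation. Sex adds about 0–1 point of power. The gain from baseline rests on two quantities the document does not give, and because entry requires predicted risk above 10%, the share already controlled could be well below 20%. A heavy covariate model would also bring its own small inflation of type I error. All of this stands. It limits the size of the point and rules out a long covariate list. It does not remove the point: the unadjusted test is a stated choice, and the covariates cost nothing to use.

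A reader might also infer something stronger from the pairing of a chi-square test with multiple imputation: that the mismatch itself loses precision, or that a chi-square run on 300 completed records with 255 observed would have a type I error of about 7%. The document supports neither. It plans multiple imputation and a risk difference with a confidence interval, and that estimate and its SE pool directly by Rubin's rules. Approximate rules for combining chi-square statistics also exist. Nothing says that completed data will be tested as if observed, and how results are combined across imputations is detail an article may leave to the analysis plan. The precision loss comes from omitting prognostic baseline values.

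**Conclusion.** The point holds as a matter of efficiency. The planned primary test is valid but leaves precision unused. With 20% controlled at baseline and phi of 0.25 to 0.50, both assumed, the variance of the risk difference would fall by about 5% to 21%, and power at about 127 per arm would rise from about 77% to about 79–86%. With few controlled at entry or a weakly prognostic baseline, the gain is 1–2 points. The upper figure is the favourable end of an assumed range, not an expectation. The shortfall in the stated sample size is a separate issue and does not make this one more serious. The change is worth making because it is cheap and because the article reports that recruitment had not begun at submission.

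**What to change.** Prespecify as the primary analysis an adjusted risk difference from a short model: arm, sex, and either baseline triple-control status or a small set of baseline component values, not both in full. Status is a function of the components, and the full set is too many terms for this sample size. Standardisation after logistic regression would serve, with a robust or small-sample-corrected SE. Take the 95% CI and the primary P value from that estimate pooled over imputations by Rubin's rules, and say so. Keep the chi-square on observed data as a supporting analysis.

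The cost is a change of wording, slightly more work in the Stata analysis already planned, and the need to fix the covariate list in advance. No new data are needed.

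### Cost per QALY is a planned outcome of a within-trial analysis, but utilities come from published data and no preference-based measure is named, so the trial cannot estimate a QALY difference from its own participants' data

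*Protocol article*

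**What the plan says.** The Outcomes section makes cost-effectiveness a secondary outcome with two ratios: "Cost-effectiveness will be assessed through incremental cost-effectiveness ratios reported as cost per participant achieving triple risk factor control and per QALY gained".

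The Statistical Analysis section fixes the source of the utilities: "QALYs will be estimated using utility weights derived from published data on health-related quality of life in Chinese adults". It then gives the type and horizon of the analysis: "A within-trial cost-effectiveness analysis will be conducted over the 12-month intervention period". The next sentence plans sensitivity analyses of the ratio to key cost and outcome inputs. Table 1 describes the assessment method for cost-effectiveness as "Economic modeling using trial data".

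The patient-reported data named elsewhere are:
- adherence: "Medication adherence will be evaluated using a self-administered online questionnaire" (Data Collection and Management);
- lifestyle and engagement: "Lifestyle modification and system engagement data will be collected through structured questionnaires" (same section);
- usability and satisfaction: "Usability will be assessed using the System Usability Scale, and satisfaction will be measured using a 5-point Likert scale" (Outcomes).

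**The concern.** A QALY difference has two ingredients: time, and the value attached to health during that time. In a within-trial analysis a reader expects both to come from the randomised participants. Here the second is imported. Participants are not asked, through any named instrument, about their health in a form that can be converted to a utility.

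Two things are at stake. First, the cost per QALY would be set partly by a choice of literature values and not by what the arms reported. Person-to-person variation in utility within the trial would not enter its uncertainty. Second, a direct effect on quality of life in either direction would go unseen: reassurance from cardiologist oversight, say, or burden from weekly messages or from added treatment. The abstract and the closing section both present the trial as a source of strong evidence on cost-effectiveness, so the basis of this ratio should be sound or plainly labelled.

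**Working it through.** The documents give no QALY figure, so there is none to reproduce. The check has two parts.

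**Part 1: is there a utility measurement anywhere?**

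| Place | What is named | Can it yield a utility? |
|---|---|---|
| Outcomes text | adherence, lifestyle, engagement, System Usability Scale, 5-point satisfaction item | No. The last two rate the system, not the person's health |
| Table 1 | the same, plus clinical parameters and modelled CVD risk | No |
| Data Collection and Management | clinical and laboratory measures, adherence, lifestyle and engagement questionnaires | No |
| Table 2 | unnamed psychosocial measures (ticked for enrollment and baseline only) | Not stated |
| Table 2 | unnamed validated questionnaires in the cost-effectiveness row (ticked at 12 months only) | Not stated |

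The two unnamed entries leave some doubt, but the Statistical Analysis section says where the utilities come from, and that is published data. CVD events and deaths are not listed outcomes, participants have no previous CVD, and the Discussion leaves long-term effects on events and mortality to future research. The weights would therefore have to attach to something the trial does record, such as risk-factor status, behaviour or estimated risk. The article does not say which.

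**Part 2: what follows when weights are imported?**

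In general, QALY difference = sum over states of (difference between arms in the proportion in the state) × (published weight for the state) × time. The trial supplies only the first factor. Two participants in the same state receive the same utility whichever arm they are in, so a direct effect within a state is zero by construction.

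The simplest illustration attaches weights to triple control or its absence.

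- Difference in control, from Sample Size Estimation: 35% − 20% = 15 points = 0.15.
- Utility gap *u* between controlled and uncontrolled: **assumed**, 0.01 to 0.05.
- Time *T*: 1 year.

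QALY difference = 0.15 × *u* × *T*:

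- *u* = 0.01: 0.15 × 0.01 × 1 = 0.0015
- *u* = 0.05: 0.15 × 0.05 × 1 = 0.0075

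If the gap builds up linearly over the year, each value is halved: 0.00075 and 0.00375.

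Under this mapping, cost per QALY = (cost per additional participant controlled) / (*u* × *T*). The multiplier is 1/0.01 = 100 at one end and 1/0.05 = 20 at the other. The ratio moves by 100/20 = 5 on identical trial data. Widening the assumed range to 0.10 makes the factor 0.10/0.01 = 10, and at a gap of zero the ratio is undefined. The size of the swing therefore reflects the range chosen; what the illustration shows is that the trial data do not constrain it.

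**The case against.** The strongest reply is that this is a disclosed and legitimate choice. The article says openly that the weights are published, and Table 1 labels the method as modelling. A modelled QALY difference can certainly be computed, so a reader who infers that the trial can produce no QALY difference at all goes too far. The limit is narrower: the trial cannot estimate one from its own participants' data.

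The planned sensitivity analyses are also a real mitigation, since a utility weight is naturally a key outcome input. They would show how far the ratio depends on the weight. They cannot supply a measured effect that was never collected.

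The sentence on utility weights might instead mean a published value set applied to participants' answers to one of the unnamed questionnaires in Table 2. That is possible but not what the text most plainly says, and no instrument is named. If it is the intention, naming the instrument and its visits would settle the point. Instrument details are often left to a fuller document, but utility data that were not collected cannot be recovered later.

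Three stronger readings are tempting and are not supported:

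- **That cost per QALY is simply cost per controlled participant divided by a constant.** This holds only under the mapping used for illustration. Weights could attach to individual risk factors, smoking or other measured characteristics. The values would still be external.
- **That the Statistical Analysis section and Table 1 contradict each other.** They do not: the first gives a 12-month horizon, and the second says that the modelling uses trial data.
- **That inpatient and emergency care are left out of the costs.** The sentence reads "Direct medical costs will include personnel time, digital intervention costs (eg, system maintenance and messaging), outpatient visits, medications, and laboratory tests", and a list introduced in that way need not be complete.

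**Conclusion.** The point holds in its limited form. As described, the plan would yield a cost per QALY that rests on externally assigned weights and cannot register a direct quality-of-life effect of the intervention. In the illustration the QALY difference is 0.0015 to 0.0075 per participant. This rests on three assumptions: that weights attach to triple control, that the gap is 0.01 to 0.05, and that it applies for the whole year. None of these is in the documents; only the 15-point difference is.

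The consequence is confined to one of two ratios within a secondary objective, which the Introduction words cautiously as an examination of potential cost-effectiveness. The primary outcome, the sample size and cost per participant controlled do not depend on it. It is a worthwhile and inexpensive improvement, not a flaw in the main comparison. It is timely because recruitment had not begun when the article was submitted.

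**What to change.** **Preferred:** add a short preference-based questionnaire, for example EQ-5D-5L, in both arms at the existing baseline, 6- and 12-month contacts. Name it in the Outcomes section and in Tables 1 and 2. Compute each participant's QALYs by area under the curve. With visits at 0, 0.5 and 1 year this is 0.5 × (U0 + U6)/2 + 0.5 × (U6 + U12)/2 = 0.25·U0 + 0.5·U6 + 0.25·U12. Compare arms with adjustment for baseline utility. The cost is a few extra items at three contacts that already take place, plus any licence registration. The trial is not sized for this difference, so the estimate may be imprecise, but the interval will show that.

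**Otherwise:** keep cost per participant achieving triple control as the within-trial ratio. Present cost per QALY only as a modelled scenario, state which participant states the published weights attach to, and list those weights among the inputs varied in the sensitivity analysis. This costs wording only, at the price of a narrower economic claim.
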